## Abstract

**Background:**

Bronchiolitis imposes the largest health care burden on non-elective paediatric hospital admissions worldwide, with up to 15 % of cases requiring admission to intensive care. A number of previous studies have failed to show benefit of pharmaceutical treatment in respect to length of stay, reduction in PICU admission rates or intubation frequency. The early use of non-invasive respiratory support devices in less intensive scenarios to facilitate earlier respiratory support may have an impact on outcome by avoiding progression of the disease process. High Flow Nasal Cannula (HFNC) therapy has emerged as a new method to provide humidified air flow to deliver a non-invasive form of positive pressure support with titratable oxygen fraction. There is a lack of high-grade evidence on use of HFNC therapy in bronchiolitis.

**Methods/Design:**

Prospective multi-centre randomised trial comparing standard treatment (standard subnasal oxygen) and High Flow Nasal Cannula therapy in infants with bronchiolitis admitted to 17 hospitals emergency departments and wards in Australia and New Zealand, including 12 non-tertiary regional/metropolitan and 5 tertiary centres. The primary outcome is treatment failure; defined as meeting three out of four pre-specified failure criteria requiring escalation of treatment or higher level of care; i) heart rate remains unchanged or increased compared to admission/enrolment observations, ii) respiratory rate remains unchanged or increased compared to admission/enrolment observations, iii) oxygen requirement in HFNC therapy arm exceeds FiO_2_ ≥ 40 % to maintain SpO_2_ ≥ 92 % (or ≥94 %) or oxygen requirement in standard subnasal oxygen therapy arm exceeds >2L/min to maintain SpO_2_ ≥ 92 % (or ≥94 %), and iv) hospital internal Early Warning Tool calls for medical review and escalation of care. Secondary outcomes include transfer to tertiary institution, admission to intensive care, length of stay, length of oxygen treatment, need for non-invasive/invasive ventilation, intubation, adverse events, and cost.

**Discussion:**

This large multicenter randomised trial will allow the definitive assessment of the efficacy of HFNC therapy as compared to standard subnasal oxygen in the treatment of bronchiolitis.

**Trial registration:**

The trial is registered with the Australian and New Zealand Clinical Trials Registry ACTRN12613000388718 (registered on 10 April 2013).

## Background

Bronchiolitis, an acute lower airway lung disease caused by respiratory viruses, is the most common reason worldwide for infants <1 year of age to be admitted to hospital. Data from the USA shows that the health care burden from infants hospitalised with bronchiolitis is conservatively estimated to be US$1.73 billion per year [1, 2]. In Australia, approximately 11,000 infants with bronchiolitis require hospital admission each year, of which 1254 (12 %) were admitted to a Paediatric Intensive Care Unit (PICU) in 2013. This equates to 17.1 % of all non-elective PICU admissions, imposing a heavy resource burden (http://www.anzics.com.au/Pages/CORE/CORE-Reports.aspx). Numerous studies over the last three decades have investigated the role of various medications in managing infants with bronchiolitis including adrenaline, steroids, salbutamol/albuterol, and hypertonic saline; none of these studies have definitively changed the outcome of the disease, the burden on health care systems, or reduced the number of PICU admissions [3].

The agreed current approach to management of infants with bronchiolitis in hospitals is focused on oxygen therapy for hypoxia, respiratory support and the maintenance of hydration [4]. Respiratory support has traditionally been the domain of intensive care settings, and has been provided through an escalation of therapy from simple oxygen delivery by nasal cannula, to non-invasive ventilation with Continuous Positive Airway Pressure (CPAP) and finally to intubation and mechanical ventilation [5–7]. These latter two strategies require highly skilled staff, are costly, and are associated with a greater incidence of adverse events including ventilator-induced lung injury, barotrauma, and potential neurotoxicity associated with sedation [8].

Over the last decade High Flow Nasal Cannula (HFNC) therapy has emerged as a new method to provide respiratory support for bronchiolitis [9]. HFNC therapy works by delivering an increased volume of air and oxygen into the nasal passages than standard subnasal oxygen therapy, using a higher flow of humidified and heated gas. These increased flow rates exceed peak inspiratory flow and thereby result in more efficient delivery of oxygen to the terminal airways. Physiological studies have demonstrated reduced work of breathing and improved gas exchange [10, 11]. However, the clinical effectiveness of HFNC therapy in bronchiolitis has only been reported in non-experimental observational studies, and there is a lack of appropriately powered randomised studies with well-defined clinically meaningful outcomes [12, 13]. Moreover, the potential impact of HFNC therapy on healthcare costs related to the management of infants with bronchiolitis has not been investigated.

Two previous clinical studies using HFNC therapy in a non-randomised design have shown a reduction in intubation rates in critically ill infants in the intensive care setting [14, 15]. Both studies, however, leave the question unanswered whether this is due to improved patient care or indeed to a higher admission rate of less sick patients. A recent retrospective study showed that HFNC therapy is similar in effectiveness to nasal CPAP when used in a Paediatric Intensive Care Unit (PICU) with 25 % of the patients requiring escalation to invasive ventilation [16]. Another study analysed the outcome of infants and children presenting to an emergency department (ED) including a range of diagnoses for respiratory distress [17]. Approximately half of the 498 patients studied presented with bronchiolitis. Infants with bronchiolitis were the least likely to require intubation in this cohort and most patients responded to HFNC therapy within the first three hours of HFNC therapy initiation.

Published reports on the use of HFNC therapy suggest a very good safety profile, including the fact that patients rarely require sedation in contrast to mask-delivered non-invasive ventilation [16]. Pilot studies have thus investigated use of HFNC therapy in general paediatric ward settings with encouraging results. A pilot study in 61 infants with bronchiolitis using a flow rate of 2 L/kg/min showed that HFNC therapy can be safely delivered in a general paediatric ward and that the PICU admission rate compared to a control group could be significantly reduced by 2.5 times [12]. This data suggests a beneficial role for HFNC therapy, and indicates that this can be safely implemented in ward settings. However, in view of the lack of high-grade evidence, there is an urgent need to perform a large multicentre randomised controlled trial on use of HFNC in bronchiolitis.

## Methods

### Study aims

To perform a randomised controlled multicentre trial (RCT) in infants aged less than 12 months (corrected age) with clinically diagnosed bronchiolitis comparing HFNC therapy to standard subnasal oxygen therapy. The primary outcome is treatment failure of HFNC therapy or standard subnasal oxygen.

Secondary outcome measures comprise (a) the rate of transfer of children to higher level care (that is, the rate of transfer from regional hospitals to tertiary centres and rate of transfer from tertiary hospitals to their onsite intensive care unit (ICU) if the primary admission is to their tertiary hospital); (b) length of stay in hospital and (c) health care costs associated with the therapy, transfer and ICU admission (including intubation rates), and overall length of stay; (d) length of oxygen therapy; (e) and measurement of adverse side effects. We hypothesise that HFNC therapy will have a lower failure proportion, reduced transfer rate, reduced length of stay, and lower health care costs associated with the treatment, in comparison to standard subnasal oxygen.

### Study design and settings

#### Design

Open label, non-blinded multi-centre, randomised controlled trial comparing respiratory support and oxygen delivery via HFNC therapy versus standard subnasal oxygen therapy in infants (corrected age) to 12 months of age admitted to hospital with bronchiolitis.

#### Setting

Emergency departments and general paediatric wards of 17 hospitals in Australia and New Zealand, including 12 non-tertiary regional/metropolitan and 5 tertiary centres. Eight hospitals will have access to on-site intensive care units that cater for infants less than 12 months of age. Patients will be recruited in both the ED and general paediatric wards of these hospitals.

#### Ethical consideration and delayed consent

The study has ethical approval for delayed consent for all except one of the participating centres, as Ethics within their State does not accept delayed consent under the Interstate Mutual Acceptance initiative (Children’s Health Queensland HREC/13/QRCH/93, New Zealand Health and Disability Ethics Committees HDEC/15/CEN/46). Informed consent will be sought from the parent or guardian of the infant by the Research Nurse, Study Coordinator, or relevant clinician as soon as possible once the infant has been stabilised and the parent/guardian has had time to adjust to the emergency environment. The parents/guardians can withdraw at any time during the study, the information already collected will be retained, to ensure the results of the study can be properly evaluated.

The trial is overseen by a steering committee responsible for the ethical and rigorous conduct of the trial in both Australia and New Zealand. Governance approval has been obtained from all study sites. A Data Safety and Adverse Event Monitoring Committee has been appointed with membership independent from the conduct of the trial.

#### Case selection

Infants meeting all inclusion and exclusion criteria will be identified at triage in all EDs. This includes identifying all patients <12 months of age with respiratory symptoms and an oxygen requirement (less than 92 % saturation for tertiary centres and less than 94 % saturation for metropolitan and regional centres). Patients who are admitted to the paediatric ward without an oxygen requirement on admission but later meet these inclusion criteria are to be recruited into the study from the ward environment.

### Definitions

All infants aged 0-12 months with symptoms of bronchiolitis (as defined by the American Academy of Pediatrics) - symptoms and signs of respiratory distress and oxygen requirements are eligible [18]. Bronchiolitis is defined as signs and symptoms of respiratory distress associated with symptoms of a viral respiratory tract infection (cough, runny nose, blocked nose, tachypnoea, recessions, nasal flaring, and cyanosis) [3]. Oxygen requirement in room air is defined according to the World Health Organisation recommendation, if transcutaneous haemoglobin oxygen saturation (SpO_2_) is <94 % in room air [19–21]. Six participating tertiary centres in our study have a lower threshold of < 92 % as their standard practice of care. In these sites a threshold of < 92 % was accepted in the randomised design, different saturation thresholds in different centres will be balanced through randomisation across all sites.

***Inclusion criteria*** are infants with a clinical diagnosis of bronchiolitis less than 12 months corrected age (≥ 37 weeks post-conceptional age) with an oxygen requirement in room air of SpO2 < 92 % for tertiary centres and <94 % for regional and metropolitan centres.

***Exclusion criteria*** include those infants with urgent need for respiratory support ( i.e. non-invasive or invasive ventilation or low level of consciousness, apnoea), cyanotic heart disease, basilar skull fracture, upper airway obstruction, craniofacial malformations and infants who are already on home oxygen therapy.

### Primary outcome definition

The primary outcome is the proportion of infants in each group with treatment failure. Treatment failure of either standard subnasal oxygen or HFNC therapy arm is defined as meeting three out of four specified failure criteria requiring escalation of treatment or higher level of care such as high acuity or intensive care. Prior to escalation of care 2 to 3 hours of observing the infant in an undisturbed environment is suggested. This time frame was based on the pilot study whereby it was clearly identified that the infants who are going to fail will do so within 2 to 3 hours [12]. In the pilot study, those who failed HFNC therapy had unchanged or increasing heart rate and respiratory rate, or worsening SpO2. Clinicians are asked to wait 2 to 3 hours prior to escalation of care, however, if they are more concerned, their clinical judgement can override the protocol if a decision is made to escalate care.

***Treatment failure*** of either standard subnasal oxygen or HFNC therapy arm is defined if three of the four following criteria are met and an escalation of treatment or level of care is requiredheart rate remains unchanged or increased compared to admission/enrolment observations,respiratory rate remains unchanged or increased compared to admission/enrolment observations,oxygen requirement in HFNC therapy arm exceeds FiO_2_ ≥ 40 % to maintain SpO_2_ ≥ 92 % (or ≥94 %) or oxygen requirement in standard subnasal oxygen therapy arm exceeds >2L/min to maintain SpO_2_ ≥ 92 % (or ≥94 %)hospital internal Early Warning Tool calls for medical review and escalation of care.

The study design utilises a ***composite primary end-point of treatment failure***, which has previously been used in a RCT of HFNC therapy vs. CPAP post extubation in neonates conducted in Australia [22].

### Secondary outcome definition

Secondary outcomes are defined as (a) the proportion of infants requiring transfer to higher acuity care, which includes admission to an on-site paediatric intensive care or transfer to a tertiary hospital; (b) length of hospital stay, including intensive care length of stay and (c) intubation rates; (e) associated health care costs for the respective therapy; (f) length of oxygen therapy and; (g) adverse events.

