#### Randomisation process

The enrolment/randomisation process has been successfully tested in the previous pilot study. Randomisation will be achieved by an opaque envelope in sequential order with an allocated infant ratio of 1:1. A computer-based randomisation will be used to allocate infants 1:1 per site. Randomisation can occur at admission or at any time during hospital stay when an oxygen requirement develops.

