### Healthcare cost analysis

A within-trial economic evaluation will be undertaken from the health care provider perspective using a cost-minimisation approach, to compare the cost of providing HFNC therapy to that of standard subnasal oxygen therapy. This approach assumes a reasonable and equivalent clinical outcome at the point of discharge to home. Resources to be measured and costed will include the number of transfers between hospitals, length of stay (in PICU and/or non-intensive stay), and resources related to use of the intervention (HFNC therapy or standard subnasal oxygen therapy). Costs will be assigned using standard costing sources [24]. The Australian refined diagnostic-related groups (AR-DRG) will be used to indicate the costs associated with each hospital admission, adjusted for length of stay in hospital and in PICU. The New Zealand centres health care costs will be analysed separately and sensitivity analysis for the different health care system will be performed. Parametric (e.g. ANCOVA) and non-parametric bootstrapping techniques will be employed to compare the costs between groups, and to estimate a confidence interval around the mean difference [25]. It is anticipated that HFNC therapy will be cost saving to the health system. The cost comparison will inform recommendations on adopting HFNC therapy for the management of bronchiolitis in clinical practice.

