#### Data analysis

Descriptive statistics will be utilised to report on the baseline characteristics of the total study cohort, as well as by site. The primary outcome measure investigating clinical treatment failure will be analysed using test of two proportions, and will be reported as the difference, 95 % confidence interval and *p*-value. The secondary outcome measure investigating length of stay will likely be non-normally distributed, and as such will be analysed using a Mann-Whitney U test; if it is normally distributed independent samples t-test will be used. Analysis of secondary outcomes includes both comparisons of measurements and proportions, using confidence intervals of differences as the major method of presentation where possible. A logistic regression analysis will be used to identify risk factors. All analyses will be by intention-to-treat. A per protocol analysis will be undertaken as a secondary analysis. Pre-specified sub-groups include; ex-preterm infants, infants with congenital heart defect, infants less than 3 months of age (corrected), infants less than 6 months of age (corrected), infants presenting to tertiary sites, infants presenting to secondary sites. Statistical significance will be set at the 0.05 level. No interim analysis will occur and no stopping rules were defined.

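### Length of stay is defined as the hospital stay although infants can be randomised at any time during it, so time that treatment cannot affect enters the comparison and costs precision

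*Protocol article*

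**What the plan says.** Study aims, item (b), gives the outcome as "b) length of stay in hospital". Secondary outcome definition gives "b) length of hospital stay, including intensive care length of stay". Neither section starts the clock at randomisation.

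Late randomisation is a deliberate recruitment route. Randomisation process: "Randomisation can occur at admission or at any time during hospital stay when an oxygen requirement develops". Case selection: "Patients who are admitted to the paediatric ward without an oxygen requirement on admission but later meet these inclusion criteria are to be recruited". No upper limit is set on the interval between admission and randomisation.

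Data analysis says that length of stay "will likely be non-normally distributed, and as such will be analysed using a Mann-Whitney U test", with a t-test if it turns out normal. No adjustment for time before randomisation is mentioned for either test.

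Healthcare cost analysis says that the Australian diagnosis-related groups "will be used to indicate the costs associated with each hospital admission, adjusted for length of stay in hospital and in PICU". It names ANCOVA as an example of the parametric methods and adds bootstrapping.

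**The concern.** For an infant admitted without an oxygen need and randomised later from the ward, the hospital stay begins before the trial baseline. That first part of the stay is fixed before allocation, so neither therapy can shorten it. Leaving it in the outcome has two consequences. It adds variation unrelated to treatment. It also lets a chance difference between arms in how many infants were randomised late, or how late, move the estimate. The same time enters cost through the per-admission costing.

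Shorter stay and lower cost are two of the four benefits hypothesised in Study aims, and Healthcare cost analysis says that the cost comparison will inform recommendations on adoption. Precision on both is therefore worth having, even though they are secondary.

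**Working it through.** **The plan's own figure.** The article states no figure for length of stay or cost. Its only sample-size figure is for the primary outcome: 10 % versus 5 %, power 90 %, type I error 0.05, 582 per group. Two-sided, pooled variance, no continuity correction:

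n = [1.960·√(2·0.075·0.925) + 1.2816·√(0.10·0.90 + 0.05·0.95)]² / 0.05² = (0.7301 + 0.4752)² / 0.0025 = 581.1, rounded up to 582.

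The figure reproduces. It does not involve length of stay, so nothing below changes it.

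**Inputs for the loss of precision.** All are assumptions, because the article gives no SD of stay, no share randomised late and no delay:
- post-randomisation stay: SD 48 h;
- delay among infants randomised late: mean 24 h, SD 24 h; zero for all others;
- share randomised late: p = 0.10, 0.25, 0.40;
- delay uncorrelated with later stay.

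**Formula.** Variance of pre-randomisation time over all infants: V = p(24² + 24²) − (24p)². Relative rise in the variance of total stay: V/48² = V/2304. Equivalent loss of sample: 1 − 1/(1 + V/2304).

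| p | V (h²) | Rise in variance | Equivalent loss of sample |
|---|---|---|---|
| 0.10 | 115.2 − 5.8 = 109 | about 5 % | about 5 % |
| 0.25 | 288 − 36 = 252 | 10.9 % | about 10 % |
| 0.40 | 460.8 − 92.2 = 369 | 16.0 % | about 14 % |

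**The middle case in other terms (p = 0.25).** The standard error is multiplied by √1.109 = 1.053. A comparison of means with 80 % power counted from randomisation falls to 76 %. The effective total falls from 1164 to 1164/1.109, about 1049.

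For chance imbalance, the SD of pre-randomisation time is √252 = 15.9 h. With 582 per arm, the standard error of the between-arm difference in mean pre-randomisation time is 15.9·√(2/582) = 0.93 h. Chance alone could thus shift the difference in mean stay by up to about 1.96·0.93 = 1.8 h either way (95 % range). The standard error of the difference in post-randomisation stay is 48·√(2/582) = 2.8 h.

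**Range over wider assumptions.** Take a post-randomisation SD of 1.5 to 3 days, 10 % to 50 % randomised late, and an exponential delay with mean 0.5 to 2 days.
- Smallest: SD 3 days, 10 % late, 0.5 day. Variance × 1.005; power 80 % to 79.8 %.
- Largest: SD 1.5 days, 50 % late, 2 days. Variance × 2.33; power 80 % to 45 %.

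**Planned test.** Mann-Whitney was simulated with 582 per arm and 3000 runs per setting. Stay was log-normal with mean 3 and SD 2 days, and 10 % shorter with treatment. Power counted from randomisation was about 83 %. Counted from admission it was 81 % (10 % late, mean delay 1 day), 77 % (25 %, 1 day), 73 % (50 %, 1 day), 69 % (25 %, 2 days) and 60 % (50 %, 2 days). With no treatment effect (25 % late, 1 day), rejection was about 5 % with either clock.

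**Sensitivity to correlation.** The added variance cancels when the correlation between pre-randomisation time and later stay equals −15.9/(2·48) = −0.17 in the middle case. A more negative correlation would make counting from admission the more precise choice.

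**The case against.** The strongest objection is that the article never says in words that stay runs from admission. A time origin for a secondary outcome is the kind of detail that a full protocol or analysis plan may set. This stands as a limit on certainty. It does not remove the point: the article does define the outcome, as the hospital stay, and the ordinary meaning of that term starts at admission. Beside a recruitment rule that separates admission from randomisation and an unadjusted test, the definition as written is a poor fit.

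Several stronger readings are tempting, and the document does not support them.
- A reader might infer bias. Pre-randomisation time is balanced in expectation, and the simulated rejection rate without an effect stays near 5 %.
- A reader might infer that infants are randomised days after admission. The text allows any time in the stay and gives no distribution of delays.
- A reader might take the reference to overall length of stay in Study aims as a definition of this outcome. It belongs to the cost item (c); the stay outcome is item (b).
- A reader might suppose that randomisation times are already recorded. Clinical observations describes measurements at enrolment, but the article does not say that the time of randomisation is captured.
- A reader might conclude that costs should simply be counted from randomisation. The costing is per admission, so splitting it would be a change of method. Whole-admission cost is also a legitimate target from the health care provider's perspective.

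It is also fair to say that length of oxygen therapy largely avoids the problem, because the need for oxygen is what triggers randomisation. That lessens the consequence but does not repair the stay outcome.

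**Conclusion.** The point holds as a minor one about precision and chance imbalance in length of stay and, through it, cost. Under the assumptions stated, the variance of stay rises by about 5 % to 16 % when 10 % to 40 % of infants are randomised late. The true loss could be negligible, or larger if late randomisation is common and delays are long. The article does not allow it to be narrowed, and the result depends on delay and later stay being roughly uncorrelated. There is no bias and no effect on type I error. The primary outcome and the 582 per group are untouched.

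**What to change.** - **Length of stay.** In Study aims, Secondary outcome definition and Data analysis, define the between-arm outcome as time from randomisation to discharge home, summed over hospitals for transferred infants. This matches the end of participation given in Time frame. Report total stay from admission descriptively by arm.
- **Cost.** In Healthcare cost analysis, keep the per-admission costing and add time from admission to randomisation as a covariate in the ANCOVA already named there. The covariate is fixed before allocation, so adjusting for it is safe.
- **What it costs.** The change to stay is one of wording. The one practical demand is a date and time of randomisation for every infant. The article reports 380 of 1400 recruited by July 2015, so for those infants it may have to be recovered from existing records if it was not captured. The sample size does not change.
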